### Home environment measures

As well as the experimental data collected at the home and lab visits, we also collect naturalistic measures of the home environment that each infant experiences in a typical day. When the infant is around 3 months old we make a day-long naturalistic recording in the home to capture the infant’s social environment and physiological responses. A researcher visits the participants’ home in the morning to fit the equipment and explain its use. The equipment records throughout the day and the parents remove it at bed/bath time for collection by the researcher the next day. Recording equipment includes: an electrocardiogram (ECG) recording device with built in triaxial accelerometer, a small head-mounted camera to capture the infant’s visual field, a room camera to capture the general space the infant is in, and a LENA (Language Environment Analysis) audio recorder (www.lena.org). During the day, the parent completes a diary recording activities and routines such as feeding and sleeping.

*The ECG and accelerometery* device is purpose-made and records for over 10 hours. It is held in a specially designed cotton baby vest which is worn next to the skin, with the ECG attached using three standard Ag-Cl electrodes in a modified lead II position. To minimise movement of the device and wires, an elasticated cotton wrap is placed over the vest to hold the equipment snugly in place.

*The baby head-camera* made by Babeyes (https://www.babeyes.com) is a small HD smart camera which is clipped to a purpose-adapted cotton hat. The camera measures 5 cm across, weighs 32g and records for 2 hours. Because of the need to minimise the size of the camera, limitations on battery life and storage space mean that it is not possible to use a camera with full-day recording capacity. Parents are provided with a total of four cameras to use throughout the day during periods when the infant is awake. Footage from the camera allows us to identify periods of face-to-face communication and so to calculate a ‘face-time index’ for each infant, giving a measure of the amount of social interaction the infant experiences during a typical day. To compliment this recording and allow us to better understand who is interacting with the infant at times when the infant camera is pointed in a different direction, a room camera has also been introduced into the protocol in the second half of data collection.

*The LENA audio recorder* is held in a purpose-made tabard worn on top of usual clothing, and records the audio environment within 1–3 metres for up to 16 hours. LENA software automatically extracts: 1) Adult word count: the number of adult words the key child hears (whether this speech is directed at the child or not); 2) Key child vocalization count: words or prelinguistic babbling sounds produced by the key child (laughing and crying sounds are not included in this category); 3) Conversational turn count: instances when the key child and an adult speak one at a time in alternating turns. The software can differentiate between live voices and electronic media such as TV or radio. These measures have been shown to be reliable in English [67] as well as in other languages such as Mandinka [68][for a brief review see 69]. In total, we aim to record 7–8 hours of an infant’s home life on a typical day.

The Home Recording Visit clothes are comfortable for the infants and allow participants to behave exactly as they would on a normal day. As the ECG vest is worn next to the skin, and the LENA tabard must be the top layer, infants can be dressed in normal clothing in between. Parents are told that the vest and LENA device can be removed from the infant for comfort when necessary (e.g., during breastfeeding, nappy changing, or when the infant is sleeping or in a car seat), but that the device should be kept close to the infant to continue the audio recording and should remain as the outer layer if additional clothing is put on the infant. Clothing and equipment are shown in Fig 3.

**Fig 3 pone.0330915.g003:**
[figure not shown]
Clothing and equipment used for home recording visits.

### Questionnaires & interviews – family

Throughout the study participating families complete questionnaires which collect information on family background and lifestyle, parental mental health, maternal diet, feelings and attitudes of parent(s) towards pregnancy and parenting, infant development, and habits and behaviours relating to infant care. Most questionnaires are completed via an online link from REDCap (https://www.project-redcap.org/), but some are asked verbally (indicated by asterisk in Table 3) while the dietary recall utilizes the Intake24 database. For the first phase of the PIPKIN study these questionnaires were sent via email as a link to parents for them to complete at home. While the intention of this was to allow parents to access the questionnaires at a time convenient to them and at their own pace to reduce participant burden, the unintentional consequence was that a significant proportion of families were struggling to notice the email and remember to complete the information without several reminders. This seemed counterintuitive to the intention of reducing participant burden as we were required to contact them more often. Therefore, from February 2024 the timing of the questionnaires was reorganised so that we could conduct these during an existing study time point with participants entering data during the visit using a research tablet. To date, this has significantly improved questionnaire completion and constructively addressed participant burden.

Purpose-designed questionnaires collect demographic, family and household information antenatally and again at 5 and 9 months. This includes information such as household make up, ethnicity, educational attainments, financial status, languages spoken in the home and medical or mental health conditions.

The *Parental Mind-Mindedness recorded interview* [70] is carried out face-to-face antenatally (32 weeks) and at the 5-month lab visit. Parents are interviewed separately and are asked to talk for 3–5 minutes about their child and their (future) relationship with him/her. Recorded responses are later coded to assess the extent to which the parent refers to their child as an individual with their own mind.

The *Expectations About Your Child questionnaire* [71] concerns parental expectations of their child’s character. Parents are asked to imagine the situations described and report in what way they think their child will react in that situation. This questionnaire is administered to both parents antenatally.

The *MacArthur Subjective Social Status Scale* [72] asks participants where they feel their family ranks within society.

*Bringing order out of chaos* [73] measures environmental confusion within the home at antenatal, 1-, 5- and 9-month time points.

The *Adverse Childhood Experience (ACE) Questionnaire* [adapted from 74] asks about possible negative experiences during the mother’s childhood.

The *Brief form of the perceived social support questionnaire* [75] and *Social Exposure* questions probe the family’s wider support network and contact with others both antenatally and across the postnatal period. The *Social Exposure Questionnaire* was devised in-house and assesses social interactions and physical contact experienced by parents over the past month.

Questionnaires probing mental health are sent to both parents and include: The *Positive and Negative Affect Schedule (PANAS)* [76] which asks participants to rate the extent to which they have felt certain positive and negative emotions over the last week; The *Perceived Stress Scale (PSS)* [77] which asks participants to rate how often they have experienced particular stress-related feelings over the last month; the *Hospital Anxiety and Depression Scale (HADS)* [78] and The *Pregnancy Related Anxiety Scale (PRAS)* [79].

At the 5- and 9-month time points both parents complete questionnaires about various aspects of parenting. The *Parental Stress Scale* [80] assesses parents’ feelings about their parenting role, while the *Comprehensive Parenting Behaviour Questionnaire* (CPBQ-0, for infants 3–11 months) [81] contains items of several existing questionnaires assessing parenting behaviour, complemented with newly developed items specifically for parents of young children. The *Maternal Confidence Questionnaire* [82] (referred to as Parental Confidence Questionnaire when applicable to fathers/partners) measures confidence in parenting skills and the parent’s assessment of their ability to recognize the infant’s needs.

The *Adult Temperament Questionnaire* (ATQ) short form is a 77-item self-report questionnaire designed to assess four constructs of temperament: extraversion/surgency, negative affect, effortful control, and orienting sensitivity [83]. ATQ is completed by both parents antenatally, and at 9 months.

The *Assessment of the Day’s Ordinariness* is asked verbally at each testing visit (2 x newborn visits, 1 month and 5 months). This questionnaire asks whether today is usual in terms of the infant’s health, mood and sleep in order to identify effects that may arise as a result of non-experimental factors.

### Questionnaires & interviews – infant

At 1, 2, 3, 4 and 9 months, parents complete questionnaires about their infant’s feeding and sleeping routines. The *Feeding Questionnaire* asks about feeding method (breast/bottle) and feeding routines. The *Sleep questionnaire* combines the *Brief Infant Sleep Questionnaire* [84], the *Sleep and Settle Questionnaire* [85], and additional questions about noise levels in the home environment. The partner version includes a subset of items from the Sleep and Settle questionnaire asking how much the parent is bothered by the infant’s sleep routines, and reasons the infant is unsettled.

The *Infant’s life and routines questions* ask about who primarily cares for the infant across the week, as well as screen time and language exposure.

*The Infant Behavioural Questionnaire (very short form)* (IBQ-R VSF) [86] measures infant temperament across three scales: positive affectivity/surgency, negative emotionality, and effortful control.

The *Infant/Toddler Sensory Profile* [87] measures an infant’s sensory processing abilities and the effect of sensory processing on the infant’s functional performance in daily life.

The *UK Communicative Development Inventory* [88] is used to assess language development at 9 months. This consists of a vocabulary checklist where parents indicate which words their child can understand, and which they can both understand and say.

The *Vineland Adaptive Behavior Scales* [Vineland-II; 89], provides a standardised measure of adaptive behaviour. Scores from the four domains (Communication, Daily Living, Socialization, and Motor Skills) can be combined to create an Adaptive Behavior Composite (ABC) score. The adaptive nature of the questionnaire is built into the logic of the online questionnaire platform so that the next item is determined by the responses to previous items.

### Medical and health details/sample collection

The *Healthy Pregnancy Questionnaire* is asked verbally at the first postnatal home visit, and covers details of the pregnancy and birth, current health status of mother and baby, and lifestyle questions such as smoking, alcohol consumption, and weight gain during pregnancy.

For the *Maternal Diet Diary* mothers are asked to record their diet for a 24-hour period using the Intake 24 app during the third trimester of pregnancy, and again when their infant is 1 and 9 months old. This is a free, open-source dietary assessment research tool, provided, maintained and developed by the Cambridge NIHR Cambridge BRC Measurement Platform at the MRC Epidemiology Unit, University of Cambridge.

*Hair samples for cortisol analysis* are collected at three time points for mothers (antenatally at around 34 weeks and at the 3-month and 5-month timepoints) and are taken by the experimenter. The hair is taken from the posterior vertex from the scalp and is cut as close to the scalp as possible. The sample is approximately the thickness of a penny at the base (~10 mg). The hair is then tied at the scalp end (in order to delineate which end is which) and stored.

*Nail samples from the infant* are collected by parents via instructions provided by the experimenter at around 3 and 5 months. Samples are placed in a collection box which is collected by researchers at the 3-month and 5-month timepoints. These collection boxes are labelled to detail the exact date on which the nail clippings were obtained.

For analysis, hair samples (∼10 mg) are placed in borosilicate tubes, washed twice in isopropanol and dried for one day. Samples are cut inside the borosilicate tubes into 1–3 mm pieces using surgical scissors, and then mixed with methanol and incubated in a sonic bath for 4 hours before being removed and placed on a shaker for one day. Samples are then centrifuged at 4000 rpm at 4 °C for 10 min. The dry extract is reconstituted in a standard assay dilution buffer and frozen.

Finally, cortisol assay HCC (hair cumulative cortisol) or NCC (nail cumulative cortisol) is quantified using previously validated and commercially produced ELISA kits designed to measure free cortisol in human saliva (Salimetrics, Inc., State College, PA). Twenty-five microliters of reconstituted sample are then run in duplicate as directed by the assay protocol. Assay output in ug/dL is converted to pg/mg.

During feasibility work we first piloted the collection of samples for cortisol analyses across a wider range of parameters, including more regular data collection points from birth to five months of age and hair sample collection for partner and infant in addition to the mother. Furthermore, we ran feasibility analyses to calculate the sample weight required for the fingernail samples from the infant. This pilot work revealed several challenges which led to an adaptation of the protocol in its current version. The hair sampling from infants and partner proved difficult due to the often lower availability of hair in young infants of this age, the lower participation rate of partners (either due to low participant engagement or low volume of hair preventing sampling) and the low number of fingernail samples available for infants (either because fingernails broke off and were lost, because parents found it challenging to collect samples or because they often forgot to carry this out at the frequent number of timepoints initially trialled). While we continue to collect fingernail samples from the infants to test the feasibility of extracting cortisol from infants, we have reduced the number of timepoints to two and furthermore expect the sample size of this part of the project to be lower and used for feasibility analyses only.

### Data analysis

Due to the large amount of data generated by the PIPKIN study over a number of timepoints and using a variety of methods, it will take some time process the data and publish the final results. Data collection will conclude by 1^st^ March 2026, and it is expected that results will be published from later that year.

### Ultrasound measures

Ultrasound data is coded frame-by-frame using offline video recordings in the Observer 15XT software programme (Noldus, the Netherlands) employing Fetal Observable System Coding Scheme (FOMS) [13] to analyse fetal behaviours, such as orofacial movements, touch movements, head movements, and observable eyeblinks. The coding process includes: i) observing each scan at full speed to become familiar with the neutral face, determine the fetal state [active/quiet, sleep/awake;, [90], and calculate the codable length of the area of interest; ii) coding the total codable footage of the scan frame-by-frame from the upper torso to the lower face and upper face respectively; iii) classifying facial gestalts based on the type (e.g., cry-face, laughter-face) and complexity (based on the number of movements that occur simultaneously); iv) calculating the relative frequency of each distinct movement and gestalt per minute to account for variations in scan length; v) measuring the duration of each movement and gestalt. All scans are coded by expert coders trained in coding 4D scans and facial expressions. To ensure consistency of codes across time and among different coders, inter- and intra-reliability checks will be applied to 10% of the ultrasound data.

### Neuroimaging measures

The fNIRS and EEG data will be pre-processed and analysed to identify statistically significant regions of brain activation, from which markers of brain function in relation to specific tasks will be extracted. The resulting data will be used to generate measures of brain function for age. Multivariate data analyses will enable the exploitation of longitudinal and cross-sectional variation in testing-age to fit growth curve models. These are valuable for providing a framework for efficient age-adjusted comparisons of differences in average trajectories according to socio-economic status, groupwise differences in variability, and also for characterizing the range of individual developmental trajectories.

*fNIRS functional connectivity:* The analysis of fNIRS functional connectivity data will involve different methods to describe functional brain networks and their developmental trajectory. One such method is the seed-based correlation approach (e.g., [91]), which involves selecting a region of interest as a seed and computing the correlation coefficient between the seed and all other brain regions. Another approach will use group-level independent component analysis with dual regression to compute spatially independent patterns of brain activity (e.g., [51, 92]). This method generates a set of group-level maximally independent spatial maps (i.e., functional networks) that can be regressed out to the subject level using spatiotemporal or dual regression to obtain subject-specific spatial maps [93]. These individual-level maps can be used to assess individual trajectories of functional connectivity development.

The primary goal of these methods would be to describe functional brain network development during the first weeks of life and study interactions between pre- and postnatal risk factors, emerging social and cognitive skills, and atypical developmental trajectories in functional connectivity. We aim to describe functional connectivity at different time points and use connectivity metrics to understand whether these could be predictive of individual cognitive/behavioural performance and variability. We also plan to investigate common organizational principles and stable individual features of functional networks across task-free and task-based paradigms, assessing variations due to task state. This approach will allow us to establish individual-specific connectivity profiles that can potentially be used as predictors of individual differences in cognition and behaviour.

*ERP analyses:* This study employs EEG event-related potential (ERP) tasks at 1 and 5 months to examine early neurodevelopmental trajectories using auditory and gaze-based paradigms, drawing on approaches from Katus et al. [56] and Elsabbagh et al. [62]. The auditory ERP analysis aims to examine habituation and novelty detection, assessing developmental shifts from intensity-driven to novelty-driven responses by measuring P3, Nc, and early components (N1, P1, N2). Based on evidence from Katus et al. [56], intensity-based P3 responses at 1 month are expected to transition to novelty-driven responses at 5 months, with stronger habituation correlating with better cognitive outcomes. The gaze ERP task assesses face orienting and processing via first-look preferences, total looking time, and ERP components (P1, N170/N290, P3, Nc), with predictions that early face biases and eye gaze processing at 1 month become more specialised at 5 months, supporting emerging social brain expertise [62,94].

*EEG resting state:* For the resting-state EEG analysis, data collected at 1 and 5 months will be used to examine functional connectivity and frontal alpha asymmetry (FAA). Functional connectivity will be measured using common methods, such as coherence, phase-locking value (PLV), or weighted phase lag index (wPLI). The maturation of connectivity patterns will be assessed between 1 and 5 months. Frontal alpha asymmetry will be analysed by comparing log transformed power in the left and right frontal areas, which may indicate early tendencies toward approach or avoidance behaviours. Stability of membership in the relative left or right frontal asymmetry groups will be assessed between 1 and 5 months.

In summary, neuroimaging data will be analysed via multiple approaches to investigate the development and variability of ERP responses and functional brain networks across the early stages of life, with the goal of identifying associations with specific and general environment factors.

### Behavioural/Neurocognitive measures

Each of the behavioural measures will be analysed according to predefined scoring systems, returning a normalized quantitative score for each infant (and where applicable, each parent, i.e., maternal interactions during PCI identified through video coding) at each age point. All questionnaire data will be analysed using standard methods according to the scoring system of each individual questionnaire.

### Home environment measures

LENA recording data will be analysed to give: Adult word count, infant vocalisation count, and number of adult-infant conversational turns. The face-time index will be calculated using the head camera to determine the proportion of recording time that the infant experiences face-to-face communication during a typical day. Infant heart rate and activity will be linked to the face-time index to examine physiological responses to social communication.

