## Methods and materials

### Recruitment and eligibility criteria

Families are recruited from Cambridge (UK) and surrounding villages, either via the Rosie Maternity Hospital where patients attending for routine 20-week ultrasound scans are given information about the study, or from the community via flyers and social media advertisements. To ensure the participant sample includes families from a range of socio-economic backgrounds, community and hospital recruitment is targeted at participants living in more deprived areas, as identified by the Indices of Multiple Deprivation. Inclusion criteria for the study are shown in Table 2, with criteria relating to the infant re-assessed at birth.

**Table 2 pone.0330915.t002:** Inclusion criteria.

Mother	Infant
• 18 years old or older • Singleton healthy pregnancy • English language level adequate to answer questionnaires and communicate with research team.	• Born between 37–42 weeks gestation • Birthweight >2.5 kg • No neurological deficits or developmental disorder diagnosed during pre/postnatal checks.

Father/partner involvement is optional but encouraged, involving completing interviews/ questionnaires and taking part in recorded parent-child interaction (PCI) sessions when available. As currently in the UK partners are less likely to be available during the first months of parental leave, we prioritise the collection of maternal data for these variables and collect father/partner data second. Participant families receive a copy of the two 4D ultrasound scans as well as gift vouchers and small gifts during the study as an incentive to continue.

Piloting of aspects of the protocol took place from February 2022 with 15 families. Recruitment to the study commenced on 1^st^ June 2022.

125 families have been recruited into the study so far. Of these, forty-one have withdrawn during the study, and there may be further withdrawals among those currently enrolled. Withdrawals primarily occur around the time of the infant’s birth (i.e., after ultrasound visits). Reasons given for withdrawals included family needs, the challenges of coping with more than one child, and time constraints.

Due to the high withdrawal rate, the original recruitment target of 120 infants has been extended to allow for further postnatal recruitment until 1^st^ November 2025, with the intention of achieving a minimum of 80 datasets relating to each study hypothesis. Data collection for all time points will conclude by 1^st^ March 2026.

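### Heart rate and activity are to be linked to a once-per-infant face-time index, which is a weak basis for conclusions about an infant's physiological response to social communication

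*Protocol article*

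**What the plan says.** The Methods section on home environment measures describes a single home recording: "When the infant is around 3 months old we make a day-long naturalistic recording in the home". Table 3 of the protocol article shows no other.

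That section describes two levels of information from the head camera. The first is time-resolved: "Footage from the camera allows us to identify periods of face-to-face communication". The second is a summary, where the stated use is to "calculate a ‘face-time index’ for each infant, giving a measure of the amount of social interaction the infant experiences during a typical day". The ECG and accelerometer are worn on the same day, and the "device is purpose-made and records for over 10 hours".

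The Data analysis section on home environment measures defines the index as "the proportion of recording time that the infant experiences face-to-face communication during a typical day". The next sentence gives the planned analysis and its aim: "Infant heart rate and activity will be linked to the face-time index to examine physiological responses to social communication".

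No passage describes comparing heart rate or activity during face-to-face periods with other periods in the same infant.

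**The concern.** A physiological response to social communication is a change in an infant's heart rate or activity between face-to-face and other periods. The predictor named for this aim takes one value per infant and is measured on one day, so it has no within-infant variation. Relating heart rate to it asks whether infants with more face time differ in heart rate from infants with less.

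The two questions can have different answers. Every infant may respond while the between-infant association is too small to see. Or no infant may respond while an association appears because something such as maturity or temperament affects both face time and resting heart rate. A null result could then be read as no response, and a positive one as a response, without support for either.

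**Working it through.** **What can be reproduced.** The article gives no power, effect size or SD for this analysis, so there is no stated figure to check. What follows illustrates the consequence of the unit of analysis.

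**Inputs.** The protocol article (Recruitment and eligibility criteria) gives the sample size, "with the intention of achieving a minimum of 80 datasets relating to each study hypothesis", so n = 80. It is borrowed, because this analysis is not listed under any of the four hypotheses. Everything else is assumed and shown as a range: a within-infant response of 2 to 5 bpm; index SD 0.05 to 0.15; between-infant heart-rate SD 5 to 12 bpm; SD of the infant-level differences 4 to 8 bpm; two-sided alpha 0.05.

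**Between-infant analysis (index as predictor).** Suppose an infant's heart rate shifts by d bpm during face-to-face time, and face time is unrelated to resting heart rate. The day-mean then shifts by d × index, so the expected slope on the index is d.

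- Correlation ≈ d × SD(index) / SD(heart rate). For 3 bpm and an index SD of 0.10: 3 × 0.10 / 10 = 0.03 at a heart-rate SD of 10, and 3 × 0.10 / 5 = 0.06 at 5.
- SE(slope) = SD(heart rate) / (SD(index) × √n). With 10 and 0.10: 10 / (0.10 × 8.944) = 11.2 bpm, against a slope of 3.
- Power = Φ(d/SE − 1.96) + Φ(−d/SE − 1.96).

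| SD heart rate (bpm) | SD index | 2 bpm | 3 bpm | 5 bpm |
|---|---|---|---|---|
| 12 | 0.05 | 5.1% | 5.1% | 5.4% |
| 10 | 0.10 | 5.4% | 5.8% | 7.3% |
| 8 | 0.15 | 6.3% | 7.9% | 13.4% |
| 5 | 0.10 | 6.5% | 8.4% | 14.5% |
| 5 | 0.15 | 8.4% | 12.7% | 26.9% |

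For heart-rate SDs of 8 to 12 bpm the range is 5% to 13%. The last row is the most favourable combination: SE = 5 / (0.15 × 8.944) = 3.73, and 5 / 3.73 = 1.34, giving 27%.

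**Within-infant contrast (face-to-face versus other periods).** SE = SD(differences) / √n; power = Φ(d/SE − 1.96).

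| SD of differences (bpm) | 2 bpm | 3 bpm | 5 bpm |
|---|---|---|---|
| 4 | 99.4% | >99% | >99% |
| 6 | 84.6% | 99.4% | >99% |
| 8 | 60.9% | 91.8% | >99% |

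**Simulation with and without a confounding trait.** 4000 runs per scenario; n = 80, heart-rate SD 10, index mean 0.25 and SD 0.10, SD of differences 6. The trait shifts resting heart rate by 3 bpm per SD of the index, a correlation of 3 / √(3² + 10²) = 0.29.

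| True response | Trait | Index analysis rejects | Within-infant contrast rejects |
|---|---|---|---|
| none | none | 5.1% | 5.3% |
| −3 bpm | none | 5.6% | 99.3% |
| none | +3 bpm per SD | 73.5% | 5.3% |
| −3 bpm | +3 bpm per SD | 64.7%, all with a positive slope | 99.5% |

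In the last row the index analysis is significant in the direction opposite to the true response. These runs show what such a trait would do; they do not show that one exists.

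**The case against.** The strongest reply is that the article says only that the measures will be linked. It names no model, no day-mean heart rate and no correlation test. The authors may intend to time-lock heart rate to the face-to-face periods, which the recordings would allow, and the section headed Analyses and data availability mentions intra-individual differences and mixed models. Part of this stands: the intended model is unknown, and leaving its detail out of an article is no fault. But the sentence names the index, defined immediately before it as a daily proportion, and no mixed model recovers within-infant information from a predictor that is constant within infants. If time-locking is intended, the predictor is misnamed.

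A reader might infer that the index analysis cannot detect a response at all. That goes too far. Without confounding the slope has the right expectation, and the difficulty is very low power under the assumed SDs.

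A reader might also infer that the within-infant contrast is certain to succeed. It is not: power falls to 61% for 2 bpm with an SD of differences of 8 bpm. Nor is the contrast free of confounding, since state, feeding or posture may change together with face-to-face contact.

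Finally, a between-infant question is legitimate. Under Hypothesis 4 the article compares mean heart rate between infants from high- and low-resource families. An association with daily face time could sit beside that, provided it is not called a response.

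**Conclusion.** The predictor and the aim in this sentence do not match. Taken as written, the analysis is a between-infant association with power of about 5% to 13% for a 2 to 5 bpm response (index SD 0.05 to 0.15, heart-rate SD 8 to 12 bpm, n = 80), and 27% at best if the heart-rate SD is as low as 5 bpm. A trait related to both measures could create or reverse it. Except for n, these inputs are assumptions; only heart rate was calculated, though the mismatch applies equally to activity.

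The documents do not support a stronger claim that the authors have committed to a particular faulty test, or that the four hypotheses or the recruitment target are affected. The point should be corrected because the stated conclusion would not follow from the stated predictor.

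**What to change.** In Data analysis, Home environment measures, state that heart rate and activity will each be compared between coded face-to-face and other awake camera periods within the same infant. A suitable model is a mixed model with an infant random intercept and slope and with period type centred within infant. Show the heart-rate model both with and without adjustment for simultaneous activity: activity may be part of the response, and adjusting for it could remove part of the effect sought.

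Report any association with the day-level index separately and describe it as between-infant. State the remaining limit, that state, feeding or posture may confound the within-infant contrast.

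The cost is analysis wording plus alignment of the camera and ECG clocks, whose feasibility is assumed here. Face-to-face periods must already be identified to compute the index, and ECG and accelerometry are recorded on the same day, so no new data or visits are needed.
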